**Conclusions:**

We anticipate that polyherbal nasal fumigation will be found to be equally as effective as polyherbal steam inhalation in the management of acute rhinitis in the pediatric population. This study may provide a standardized, herbal, safe, and cost-effective treatment for rhinitis in children in the form of *dhoopana*.

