### Hypothesis

The alternate hypothesis is that *dhoopana* has equivalent efficacy to polyherbal steam inhalation in reducing the signs and symptoms of *pratishyaya* in children aged 7-14 years. The null hypothesis is that *dhoopana* does not have equivalent efficacy as polyherbal steam inhalation in reducing the signs and symptoms of *pratishyaya* in children aged 7-14 years.

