### Trial Design

This will be a randomized, reference, controlled, open-label equivalence clinical study. A total of 70 patients have been recruited for the study.

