### Sample Size

A comparative pilot study was performed with 20 patients, including 10 patients in 2 groups, to evaluate the efficacy of *dhoopana* for rhinitis in comparison with polyherbal steam inhalation. Based on the results of that study, the minimum sample size for this study was calculated by using the following formula of proportion:

The parameters related to sample size were as follows: α=.05; β=.2; proportion in group 1=0.60; proportion in group 2=0.90; ratio (group 2/group 1)=1; minimum sample size needed for group 1=32; and minimum sample size needed for group 2=32. The minimum total sample size needed was 64, and the minimum total number of patients to be enrolled was 35 in each group (including a 10% withdrawal rate).

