### Data Analysis

Data will be analyzed by using appropriate descriptive and inferential statistics. Quantitative variables will be analyzed with the Student *t* test and subjective parameters will be analyzed with the Wilcoxon signed test and Mann-Whitney *U* test. Alternate statistical methodologies may be applied if deemed necessary.

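### The tests named cannot, in their ordinary use, support the equivalence hypothesis; the article states no margin and sizes the trial to detect a difference

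*Protocol article*

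**What the plan says.** Trial Design calls the trial a "randomized, reference, controlled, open-label equivalence clinical study". Under Hypothesis, the alternative is that dhoopana "has equivalent efficacy to polyherbal steam inhalation in reducing the signs and symptoms of" pratishyaya, and the null is that it "does not have equivalent efficacy as polyherbal steam inhalation in reducing the signs and symptoms of" pratishyaya. The Conclusions paragraph of the abstract anticipates that fumigation "will be found to be equally as effective as polyherbal steam inhalation in the management of acute rhinitis in the pediatric population", and the Discussion repeats that expectation.

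Data Analysis assigns quantitative variables to the Student *t* test and says that "subjective parameters will be analyzed with the Wilcoxon signed test and Mann-Whitney" *U* test. It adds: "Alternate statistical methodologies may be applied if deemed necessary". Sample Size lists "α=.05; β=.2" and "proportion in group 1=0.60; proportion in group 2=0.90; ratio (group 2/group 1)=1", which lead to 32 per group and 35 enrolled per group. The article gives no equivalence margin, no confidence-interval rule and no two one-sided tests.

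The Methods paragraph of the abstract gives the primary outcome as the change in TNSS and a modified cold spatula test. Results says that 66 patients will be analysed.

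**The concern.** In an equivalence trial the burden of proof is reversed. The data must exclude differences as large as the margin before equivalence can be claimed. The usual *t* and Mann-Whitney tests put the burden the other way: they start from no difference and look for evidence against it. A significant result shows a difference. A non-significant one shows only that the data did not settle the matter. Neither outcome rejects the null that this article states, and without a margin that null has no numerical meaning.

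The primary conclusion is at stake. If non-significance were taken as proof of equal effectiveness, a less effective treatment could pass. It would pass more easily the smaller or noisier the data, which is the opposite of what a sound criterion should do.

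**Working it through.** **1. Inputs.** From Sample Size: two-group rates 0.60 and 0.90, α = .05, β = .2, ratio 1, stated result 32 per group. From Withdrawal Criteria and Stoppage: 2 withdrawn in each arm, so 35 − 2 = 33 per arm and 66 in all, which agrees with Results. The article does not say whether α is one- or two-sided.

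**2. The stated sample size.** With pooled variance under the null, two-sided α and no continuity correction:

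n = [1.960·√(2·0.75·0.25) + 0.842·√(0.60·0.40 + 0.90·0.10)]² / (0.90 − 0.60)² = [1.200 + 0.483]² / 0.09 = 31.5, so 32 per group.

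This matches exactly. A one-sided version with continuity correction also gives 32. Both are tests to detect a difference, and neither contains a margin.

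**3. Hypotheses against tests.**

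| Item | What it addresses |
|---|---|
| Stated null | The arms are not equivalent |
| Student *t*, between arms, ordinary use | Null: mean difference is zero |
| Mann-Whitney *U*, ordinary use | Null: no difference in distribution between arms |
| Wilcoxon signed | Null: no change within a group; does not compare arms |
| Sample size | Detecting a 30-point difference |

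No result in the middle three rows rejects the first row.

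**4. How often would P>.05 occur with 33 per arm?** For proportions, two binomials were enumerated with a pooled z test at two-sided .05. For means, a noncentral *t* with 64 df was used, with noncentrality δ·√(33/2).

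| True situation | Source | P(P>.05) |
|---|---|---|
| 60% v 90% | Sample Size | .158 |
| 70% v 90% | assumed | .451 |
| 75% v 90% | assumed | .631 |
| 0.5 SD | assumed | .484 |
| 0.3 SD | assumed | .775 |

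The proportion rows follow the scale on which the trial was sized, although Data Analysis names no test of proportions. The SD rows relate to the *t* test. The Mann-Whitney test was not computed separately.

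**5. What could 33 per arm show against a margin?** The article gives none, so these margins are assumed. With a true difference of zero and two one-sided 5% tests, approximate power is 2Φ(m/√(2/33) − 1.645) − 1, with m in SD units:

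- m = 0.5: 2Φ(2.031 − 1.645) − 1 = .30
- m = 0.7: .77
- m = 0.8: .89

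**The case against.** Several stronger readings are tempting, and the article does not support them.

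- **That P>.05 will be read as equivalence.** No section says so. The Conclusions paragraph and the Discussion state an expectation, not a criterion. It can only be said that the article describes no other route from its tests to that expectation.
- **That no margin exists anywhere.** This is a condensed article, and a full protocol or SAP may hold one. The supportable statement is that the article gives none and that its listed sizing parameters contain none.
- **That a *t* test can never serve.** Two one-sided tests are themselves *t* tests against shifted nulls. The criticism applies to the ordinary zero-difference use, which is the natural reading when no shift or margin is given. The open sentence on alternate methods could admit such an analysis, but it names no method and no margin.
- **That the 45% to 78% figures are error rates to set against 5%.** They rest on assumed differences. With a generous margin, 0.3 SD might be acceptable, and then non-significance there would be no error.
- **That the trial is too small.** This depends entirely on the margin: at 0.8 SD, 33 per arm would be enough for 80% power.

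One part of the concern survives all of this. The article is not silent on the analysis: it commits to hypotheses, tests and a sizing, and the last two do not fit the first. An analysis plan would have to overturn what is written here, not merely add detail.

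**Conclusion.** The point holds as an internal contradiction and must be fixed. The stated hypotheses are those of an equivalence trial, while the named tests and the sample size are those of a difference trial. As written, no result of the named analysis can support the alternative hypothesis.

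The size of the problem is conditional. If non-significance were taken as equivalence, a 30-point deficit of the kind used for sizing would pass about one time in six. The smaller assumed deficits would pass between 45% and 78% of the time. These figures assume 33 analysed per arm and two-sided .05. How many of those passes would be wrong cannot be said until a margin is set.

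**What to change.** Before outcomes are tabulated by arm:

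1. Fix a symmetric equivalence margin for each primary outcome: TNSS change in score points and modified cold spatula fogging area in its own units. Justify each as a clinically negligible difference. Alternatively, name one of the two as the single primary. If both stay, state whether both must be met.
2. Make the 90% confidence interval for the between-arm difference (two one-sided 5% tests) the primary analysis. Conclude equivalence only if the whole interval lies inside the margin.
3. State that a non-significant *t* or Mann-Whitney result is not evidence of equivalence, and that the Wilcoxon signed test describes within-group change only.
4. Limit the sentence on alternate methods to sensitivity analyses.

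This needs no new patients, only revised wording and a justified margin for each primary outcome. There are two real costs. First, the trial may end inconclusive; at an assumed margin of 0.5 SD it would have about 30% power. Second, enrolment is already complete in an open-label trial, so the margin must be reported as set after enrolment closed. If outcomes by arm have already been seen, that must be reported too.

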**Methods:**

A total of 70 participants fulfilling the inclusion criteria were selected and distributed into 2 groups of 35 each. The intervention group received *dhoopana* and the control group received polyherbal steam inhalation, both twice daily for 7 days. The primary outcome measure was the change in Total Nasal Symptom Score and a modified cold spatula test. At the same time, the association between *prakriti* (body constitution) and the prevalence of *pratishyaya* in children was analyzed as a secondary outcome. Assessments were performed on days 3, 5, and 7, with a follow-up time of 28 days. Appropriate descriptive and inferential statistics will be used for data analysis.

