## Methods

### Recruitment

The patients were selected from the outpatient and inpatient departments of the Department of Kaumarabhritya (Ayurvedic pediatrics) of Mahatma Gandhi Ayurveda College, Hospital & Research Centre and from the surrounding region. After initial screening, the patients were randomized using computer-generated random numbers into 2 groups; the control group (polyherbal steam inhalation) and the intervention group (polyherbal nasal fumigation). All baseline parameters were recorded at the start of the study. Both groups underwent treatment for 7 days. All the parameters were recorded on the third, fifth, and seventh days, with a follow-up of 28 days after the treatment period. Patients were advised to drink warm water and stay away from cold and sour items. Patients were given regular counseling and reminders through calls or messages to follow the rules and regulations of the trial.

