**Additional symptoms as per Ayurveda texts**			
	* **Sirashoola** * **(headache)**		
		No headache	0
		Occasional headache	1
		Frequent headache	2
		Continuous headache	3
	* **Aruchi** * **(loss of appetite)**		
		Absent	0
		Present	1
	* **Kasa** * **(cough)**		
		No cough	0
		Occasional cough	1
		Moderate cough	2
		Continuous cough with throat and chest pain	3

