#### Objective Criteria

The modified cold spatula test will be used to measure nasal patency in rhinitis. The test is done to study the area of fogging associated with a nasal obstruction and compare the pre- and posttreatment outcomes. The patients are asked to breathe normally over a polished stainless steel plate, and the extent of fogging is marked with a marker pen. The magnitude of fogging is then measured with a transparent graph sheet marked with a central red line at 50 mm on the x-axis, dividing the graph into 2 equal parts with corresponding right and left areas of fogging.

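### The named between-arm tests leave out the recorded baseline, which gives up precision that an equivalence trial of 66 children could recover at almost no cost

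*Protocol article*

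**What the plan says.** The Methods part of the Abstract states that "The primary outcome measure was the change in Total Nasal Symptom Score and a modified cold spatula test". The Trial Design section states that "This will be a randomized, reference, controlled, open-label equivalence clinical study".

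Under Data Analysis, "Quantitative variables will be analyzed with the Student *t* test", and "subjective parameters will be analyzed with the Wilcoxon signed test and Mann-Whitney *U* test". The symptom score is listed under Subjective Criteria, so its between-arm test is the Mann-Whitney U. Fogging area in the cold spatula test is listed under Objective Criteria and is a measured area, so it falls to the t test. The section names no covariate. It ends by allowing other methods if they are thought necessary, with no condition attached.

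The Recruitment section says "All baseline parameters were recorded at the start of the study" and "Both groups underwent treatment for 7 days". Assessments followed on days 3, 5 and 7, with a 28-day follow-up. No visit is named as primary. The Objective Criteria section says that fogging is used to "compare the pre- and posttreatment outcomes", but neither that section nor Data Analysis says whether the arms are compared on change or on the post-treatment value.

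**The concern.** The pre-treatment value usually predicts the later value of the same measure, and on a score bounded at zero a child cannot improve by more than the baseline. A two-sample test on change corrects for baseline with a fixed slope of one. A test on day-7 values does not correct at all. ANCOVA estimates the slope from the data and, apart from one lost degree of freedom, is at least as precise as either.

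This matters more here than in a superiority trial with a generous sample. An equivalence conclusion depends on how narrow the interval for the arm difference is. Recruitment is finished, so more patients cannot supply that precision. The baseline values are already in hand.

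**Working it through.** **Sample size.** The article's own figure is 32 per group for 0.60 against 0.90 (α = 0.05, β = 0.2). With a pooled two-sided test: [1.96·√(2·0.75·0.25) + 0.8416·√(0.24 + 0.09)]² / 0.30² = (1.200 + 0.483)² / 0.09 ≈ 31.5, so 32, which matches. Adding 10% gives 35.2 (32 × 1.1) or 35.6 (32 / 0.9), against 35 stated. This calculation compares proportions, so it gives no SD or correlation and the point below does not alter it.

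**Inputs.** 35 enrolled per arm less 2 withdrawn per arm = 33 per arm, 66 in all (Withdrawal Criteria; Results). The correlation r between baseline and day 7 is an assumption: 0.3, 0.5, 0.7. The ratio k of day-7 SD to baseline SD is also an assumption: 1, 0.75, 0.5.

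**Standard errors of the arm difference** (√(2/33) = 0.246):
- change: √(SD0² + SD1² − 2r·SD0·SD1) × 0.246
- day-7 value, unadjusted: SD1 × 0.246
- ANCOVA: SD1·√(1 − r²) × 0.246

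**Equal SDs (k = 1), in SD units.** ANCOVA against change is √((1 + r)/2); against day-7 values it is √(1 − r²).

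| r | 90% half-width: change | day-7 value | ANCOVA | narrower than change | narrower than day-7 |
|---|---|---|---|---|---|
| 0.3 | 0.486 | 0.411 | 0.392 | 19% | 5% |
| 0.5 | 0.411 | 0.411 | 0.356 | 13% | 13% |
| 0.7 | 0.318 | 0.411 | 0.293 | 8% | 29% |

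To match ANCOVA with 33 per arm, a change analysis would need 33 × 2/(1 + r) = 51, 44 or 39 per arm. A day-7 analysis would need 33/(1 − r²) = 36, 44 or 65.

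**Smaller day-7 SD** (baseline SD set to 2).

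| k | r | SE change | SE day-7 | SE ANCOVA | ANCOVA v change | of which: day-7 v change |
|---|---|---|---|---|---|---|
| 0.75 | 0.3 | 0.519 | 0.369 | 0.352 | 32% narrower | 29% narrower |
| 0.75 | 0.5 | 0.444 | 0.369 | 0.320 | 28% narrower | 17% narrower |
| 0.75 | 0.7 | 0.352 | 0.369 | 0.264 | 25% narrower | 5% wider |
| 0.5 | 0.3 | 0.480 | 0.246 | 0.235 | 51% narrower | 49% narrower |
| 0.5 | 0.5 | 0.426 | 0.246 | 0.213 | 50% narrower | 42% narrower |
| 0.5 | 0.7 | 0.365 | 0.246 | 0.176 | 52% narrower | 33% narrower |

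In five of the six rows, more of the gain over change comes from no longer subtracting baseline than from adjusting for it. Against day-7 values the gain stays at 5%, 13% and 29% whatever k is.

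**Rank test.** The closed forms describe mean comparisons, so they apply directly to the t test on fogging area. For the symptom score, a simulation of bounded integer scores (0–12, baseline mean 6 and SD 2, near-equal SDs, true shift 1.25 points, 33 per arm; all assumed) gave power for a difference of 54%, 67% and 87% for Mann-Whitney on change and 74%, 81% and 93% for ANCOVA at r = 0.3, 0.5, 0.7. Table 4 also lists "Additional symptoms as per Ayurveda texts"; scoring all items (0–19) gave similar results. ANCOVA type I error stayed at 4.2–5.4%, with up to 34% of children at zero on day 7.

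**The case against.** The strongest reply is that nothing here is wrong. Unadjusted tests are valid in a randomised trial, a condensed article may leave covariates to a fuller document, and the clause on alternative methods does not exclude ANCOVA. Validity is conceded. But the article does more than stay silent: it names the tests, and the open clause secures nothing, because it does not say when or how it would be used.

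The second reply is that the size is uncertain. This stands. No SD, correlation or margin is given, and the benefit depends on which unadjusted comparison is meant. A reader who assumes change scores might infer that ANCOVA halves the interval, or that it lifts equivalence power from 6% to 37% (assumed margin 1 point, SD 2, r = 0.3, k = 1). The documents do not support that as the value of adjustment: on unadjusted day-7 values the same power is already 30%. With a 2-point margin, power is at least 93% under each of the three analyses, so little is left to gain.

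The third reply is that changing the primary test after enrolment in an open-label trial invites suspicion, and that a linear model is an imperfect fit to a short bounded ordinal sum. Both stand as costs. Nor do the documents make day 7 the primary visit. It is the natural choice because treatment lasts seven days, but the same model works at any visit.

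**Conclusion.** The point holds as a missed gain in precision. It is not an error, and no bias or inflated type I error should be inferred. With 33 per arm and r assumed between 0.3 and 0.7, adjustment narrows the interval by about 19% down to 8% relative to change scores with equal SDs, and by about 5% up to 29% relative to unadjusted day-7 values. The gain over change scores is larger if the day-7 SD is smaller, though mostly for the separate reason shown in the working. Which figure applies cannot be settled from the article.

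A reader might also infer that ANCOVA would make the equivalence claim sound. It would not: equivalence needs a prespecified margin against which the interval is read, and the article gives none. That gap is the more serious one. Adjustment only affects how small a margin 66 children could support.

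**What to change.** Before the data are analysed, and with a date showing this, replace the between-arm part of Data Analysis with wording such as:

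*The arms are compared on the Total Nasal Symptom Score at the end of treatment (day 7) by the adjusted mean difference from an ANCOVA with arm and the baseline score, reported with its confidence interval. Fogging area is analysed in the same way with its own baseline. Mann-Whitney U and Student t tests are reported as sensitivity analyses.*

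If another visit is named primary, substitute it for day 7. If analysis has already begun, keep the named tests as the main comparison and report ANCOVA as supportive.

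The cost is a few sentences and two regression models on data already collected, with no change to treatment, visits or sample size. The drawbacks are a late change in an open-label trial, which must be documented, and a linear model for a bounded ordinal score, which the retained rank test helps to check. The equivalence margin has to be set separately.

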### Ethical Considerations

The study obtained approval from the institutional ethics committee of Mahatma Gandhi Ayurved College Hospital and Research Centre (MGACHRC/IEC/JULY-2022/522). The committee will decide on the end point and oversee the trial as it progresses. The researchers will assess any adverse events and will report to the ethics committee. Consent from parents and assent from patients was obtained before conducting the trial in the local language while explaining every aspect of the study. The informed consent form included a patient information sheet (part 1) and a certificate of consent (part 2). Data will be anonymized and personal information of the participants will be kept confidential before, during, and after the trial. Physical data will be stored in a protected storage facility with access available only to the researchers. Computerized data will be held in a password-protected hard drive with access available only to the researchers. There was no need to provide any compensation to the patients in the trial. Identification of individual participants and users will not be possible in any images in the manuscript or supplementary files. If needed, prior consent will be obtained from identifiable individuals before the inclusion of such images.

### Withdrawal Criteria and Stoppage

No adverse effects of the trial drug were noted during the treatment period. Thus, no cases were excluded from the study. A total of 4 patients, including 2 patients in each group, voluntarily stopped taking treatment during the trial and were counted as withdrawn.

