Sebastian and Sujatha [20]	The study showed that steam inhalation with *tulsi* leaves is effective in relieving symptoms of coryza compared to hot water steam inhalation in children aged 6-12 years.	The study was performed in a selected community with a small sample size, and no randomization was done. Steam inhalation was administered for only 3 days. The follow-up time was not mentioned in the article. This study is a randomized clinical trial, and *tulsi* along with *nilgiri*, *nirgundi* and *vasa* will be used for steam inhalation in the control group for 7 days with a follow-up of 28 days.
Macchi et al [21]	A statistically significant improvement was seen in ciliary motility in the first group, who received a nasal wash with sodium hyaluronate in saline solution (*P*<.001).	This was a pilot study with very small sample size. Moreover, the study included patients with recurrent upper respiratory tract infections; there was no specific disease chosen for the study. Aerosol use was indicated in lower respiratory tract infection, as there was a chance of the medicine entering the lungs. In our study, only *pratishyaya* cases will be included, rather than all patients with respiratory tract infections. Polyherbal fumes will be administered in the trial group, which could be a better alternative to aerosols.
Baartmans et al [22]	Annually, on average 3 people are admitted to a Dutch burn center for burns resulting from steam inhalation therapy. Most patients are children, and they need skin grafting more often than adults. At burn centers in the Netherlands, 31 patients were admitted with burns caused by steam inhalation therapy in the 1998 to 2007 period.	These data show that steam inhalation can result in burns, especially in children. So, in our study, we plan to find if *dhoopana* can be an alternative.
Murphy et al [23]	Between July 1 and December 31, 2002, 7 children were admitted to the burn unit of a children’s hospital in Dublin with scalds sustained during the course of steam inhalation. The children ranged in age from 9 months to 10 years. Techniques involving kettles or bowls of boiling water should be actively discouraged.	The common technique of steam inhalation is risky in children as it may cause burns. So, in our study, we plan to find an easier way to administer herbal effects to the nasal mucosa through *dhoopana*.

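### The article's only safety result covers effects of the trial drug during treatment, so it does not address procedure injuries or follow-up events

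*Protocol article*

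**What the plan says.** The article's one safety result stands under Withdrawal Criteria and Stoppage: "No adverse effects of the trial drug were noted during the treatment period". It draws a consequence from this: "Thus, no cases were excluded from the study". It then says that four children, two per group, "voluntarily stopped taking treatment during the trial and were counted as withdrawn". No reason for stopping is given.

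Ethical Considerations states a wider plan: "The researchers will assess any adverse events and will report to the ethics committee". That sentence sets no limit by cause, arm or period.

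On timing, Recruitment says "Both groups underwent treatment for 7 days", "with a follow-up of 28 days after the treatment period".

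On the hazard of the comparator, Table 1 in the Introduction lists two reports of children burned or scalded during steam inhalation. It remarks on one of them: "These data show that steam inhalation can result in burns, especially in children". The table offers this as a reason to look for an alternative. Steam is the control treatment (Table 2), and parents were trained to give both treatments at home (Drug Collection and Authentication).

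The abstract's Conclusions hope for a safe treatment. The Discussion calls fumigation safe and suggests that it could be preferable to steam.

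**The concern.** The plan is to assess every adverse event, but the result as printed covers a smaller class: effects attributed to the trial drug, within the treatment period. Two kinds of event that matter to the trial's rationale are not clearly inside that class.

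The first is injury from the delivery procedure. A burn or scald from hot water or steam is not naturally an effect of a drug, yet it is the harm that the article names when it argues for an alternative to steam. The second is anything that arises after the last treatment day.

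Attributing an event to a drug is also a causal judgement. In an open-label trial it is made by people who know the allocation. Counting events whatever their presumed cause removes that judgement from the count.

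At stake is what the trial can say about safety. The printed sentence would read the same whether or not a procedure-related burn or a follow-up event had occurred, so it cannot carry a conclusion that fumigation is safe or a better option than steam.

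**Working it through.** The point rests on the scope of wording, and there is no published safety figure to recompute. The article gives a zero without a denominator.

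**1. Scope, side by side**

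- *Cause.* Plan (Ethical Considerations): any adverse event. Result (Withdrawal Criteria and Stoppage): effects of the trial drug.
- *Period.* Plan: no limit. Result: the treatment period only.
- *Arm.* Plan: no limit. Result: unclear. The term trial drug is undefined. The Exclusion Criteria use it for all children before allocation, and both preparations contain the same four herbs, so it may cover both arms. Even then it names a product and not the way it is delivered.
- *Denominator.* Not given for the result.

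**2. Share of observation covered**

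Inputs from Recruitment: 7 treatment days and 28 days of follow-up after them.

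- Total observed: 7 + 28 = 35 days.
- Outside the statement: 28/35 = 80%.

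**3. Counts**

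- Stops: 2 + 2 = 4.
- Patients to be analysed: 70 − 4 = 66, as the Results section says. A safety table on those 66 would leave out the four children who stopped.

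**4. What a zero would rule out, even if it applied to all events**

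The exact one-sided 95% upper limit for zero events in n children is 1 − 0.05^(1/n).

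- One arm, n = 35: 1 − 0.05^(1/35) = 8.2%.
- Both arms, n = 70: 1 − 0.05^(1/70) = 4.2%.

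The chance of seeing no event in 35 children is (1 − p)^35. The documents give no event rate, so p is assumed over a range.

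- p = 1%: 0.99^35 = 70%.
- p = 2%: 0.98^35 = 49%.
- p = 5%: 0.95^35 = 17%.

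A zero is therefore weak evidence even at its widest reading, and the printed reading is narrower.

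**The case against.** The strongest reply is that the sentence explains why nobody was removed from the study and is not a safety definition. Safety is not among the objectives or outcomes, results are still to be published, and Ethical Considerations already commits the researchers to assessing any adverse event, which would include a scald. A journal article also leaves adverse event definitions and collection windows to the full protocol and case record form.

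Much of this stands. The gap lies in how the result is worded and not in the whole safety plan, and missing definitions are not the complaint. But the article does print a safety result, its scope is narrower than the stated plan, and safety conclusions are anticipated elsewhere in the same article.

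It is also fair to say that the time limit has little bearing on scalds. They would happen during administration, hence within the 7 days. The time limit matters for other events; for scalds it is the restriction to drug effects that matters.

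A reader might go further in three ways that the documents do not support.

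- *That control-arm events are excluded.* The term trial drug is undefined and may cover both preparations.
- *That the four stops hide intolerance, or that the article treats them as unrelated to tolerability.* It says only that they were voluntary. The children stopped taking treatment, so the stops most naturally fall within the treatment period, and a drug effect as the reason would be inside the statement and denied by it. What is left is that no reason is given, so procedure-related reasons or lack of effect are not ruled out. The stops are equal between arms, so they suggest no difference.
- *That the abstract and Recruitment disagree on follow-up.* The abstract's "with a follow-up time of 28 days" reads as a short form of the fuller wording in Recruitment.

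**Conclusion.** The concern holds in a limited form. The printed safety statement is narrower than the article's own plan to assess any adverse event. It leaves 28 of 35 observed days (80%) unaddressed and does not naturally cover injuries from the procedure, including the burns cited as a reason for the trial. It therefore cannot support conclusions that fumigation is safe or preferable to steam.

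It does not follow that any burn, scald or follow-up event occurred, or that one was known and left out; nothing in the article shows this.

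The 80% rests on reading follow-up as 28 days after a 7-day treatment period, as Recruitment states. The upper limits of 8.2% and 4.2% assume a true zero for all events on full denominators of 35 and 70, which the article does not claim. The correction is worth making before results are published, because it changes what the trial can conclude on safety at little cost.

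**What to change.** Bring the statement under Withdrawal Criteria and Stoppage into line with Ethical Considerations, and carry the same scope into the results paper:

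- Report all adverse events in both arms regardless of presumed cause, naming burns, scalds and other procedure-related events explicitly.
- Cover the time from first administration to the last follow-up contact.
- Use all 35 children per arm as the denominator, not the 66 to be analysed.
- Give the reason for each of the four stops where it is recorded, and say so where it is not.
- If the count is zero, print it with its denominator and upper confidence limit.

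The cost is a re-reading of existing case records and revised wording, with the possibility of a less favourable safety figure. No treatment, schedule or clinical rule changes.
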